| **6. Materials and Methods** (that could best achieve the study objectives)  **6.1 Study area/setting** (description of the area or setting where the study will be conducted)  The study will be carried out in two villages in eastern Sudan. These villages have relatively stable conditions and no modifications in the applied control measures are expected. They are far from each other and matched for malaria burden, environmental factors and control measures.  The whole area is characterized by seasonal malaria transmission. The season is confined to three months of the year, October – December. The main malaria parasite is *P. falciparum* and the main mosquito vector is *Anopheles arabiensis*10. Subpatent parasitaemias persist in some individuals throughout the dry season, with re-appearance of clinical symptoms in the malaria season associated with reinfection11.  **6.2 Study subjects** (eligibility and exclusion criteria for the study subjects)  The whole residents of the two villages will be recruited into the study. The following ones will be excluded from drug testing :   - pregnant women - children < 3 year old - history of allergy to sulpha drugs - infection with *Plasmodium* species other than *falciparum*   6.3 Combination Therapy:  The antimalarial drug combinations would be: Artesunate (AS) + Sulphadoxine Pyrimethamine (S/P) + primaquine (single dose of 0.75 mg of base/kg body weight) for one group and AS + S/P for the other. These are intended to treat malaria cases, sub-patent parasitaemia and gametocyte carriage. AS and S/P are blood schizontocidal drugs active against *P. falciparum* and gametocytocidal against developing gametocytes of *P. falciparum*. The addition of premaquine is expected to clear mature gametocytes.    6.4 Study design  A community-based intervention study will be conducted in the two villages. The study will start by a baseline evaluation of malaria morbidity and mortality during the transmission season of 2003.  A cross-sectional clinical, parasitological and molecular survey will be carried out during the dry season of 2004. Villagers will be screened for malaria parasite by microscopy. Samples detected negatives by blood films will be screened by conventional nested PCR *Pfs25* primers for detection of sub-patent parasiteamia. Blood will be collected from individuals detected positive by PCR for detection of gametocyte using the RT-PCR technique.  A treatment trial will then be carried out on malaria cases and asymptomatic carriers at the end of the dry season to test the efficacy of two combinations of antimalarial drugs.They will be followedup on days 3, 7 and 14 to confirm the clearance of *P. falciparum*  sub-patent parasitaemia and gametocyte carriage.  The impact of treating sub-patent parasitaemia and gametocyte reservoir on malaria morbidity and mortality will then be evaluated by carrying out a post-intervention survey in the two villages during the next transmission season.  **6.5 Sample sizes**  **6.5.1 Sample size for detection of parasite positive individuals during the dry season:**  The prevalence of sub-patent parasitemia during the dry season is expected to be about 15%. Therefore, the whole two villages will be screened during the dry season for detection of all positives including microscopical cases and subpatent parasitaemia to give the sample size needed for treatment trial.  **6.5.2 Sample size for evaluation of the efficacy of the two combinations**  A trial with 55 subjects on each arm would have 90% power (using a significance level of 0.05) to detect a difference between treatment groups if gametocyte prevalence detected by RT-PCR after treatment is 20% or more on day 3 in AS/SP combination and 5% or less in AS/SP + PQ, allowing for 10% loss to follow up. From earlier surveys the prevalence of sub-patent parasitaemia in the dry season was expected to be about 15% therefore 650 residents of all age groups had to be screened |

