|  |
| **6.5.3 Sample size for detection of the impact of treatment on malaria morbidity and mortality**  Based on the previous records the prevalence in the two villages is expected to be around 10%. Therefore, 216 residents from each village, out of the total of 500, will be examined to detect prevalence between 5 - 15 % at 5% level of significance with a design effect of 2.  The sample sizes were calculated using Epi-Info 2002 computer programme.  6.6. Sampling technique and randomization  Persons who were positive by PCR in the dry season will be enrolled in the study for measuring the efficacy of each combination. The list of eligible participants will be sorted according to village and age, to achieve an implicit stratification. The allocations for this ordered list will be generated using restricted randomization with a block size of 12 in Stata version 7 (Statacorp, Texas)  Simple random sampling technique will be used for the selection of the sample size needed for detecting the impact of the treatment on malaria morbidity.  6.7. Data Collection methods, instruments used, measurements  6.7.1.Describe the instruments used for data collection (questionnaire,observation recording form, etc..), studied variables included in these instruments, and methods used to test for the validity and reliability of the instrument.   - Clinical data will be collected by a medical doctor using a questionnaire. - Thin and thick blood films will be collected on slides by finger brick - A parallel drop of blood will be collected on filter paper from the same finger brick for screening by conventional nested PCR technique. - Microvet tubes will be used to collect 150 ul of blood by finger brick from PCR positive individuals only. Samples will be used for detection of subpatent gametocytes by RT-PCR.     6.7.2.Techniques used should be briefly described and referenced  Thin and thick blood films will be stained and used for species identification and parasite density estimation13.  **Detection of low level *P. falciparum* infection during the dry season**  *P. falciparum* DNA will be extracted from filter papers of microscopically negative blood samples14.  Nested PCR will then be used to detect low level *P. falciparum* infections that prevail during the dry season15. Principal genes to be detected are *Pfs*25 and *Pfg*377, which encode gametocyte specific proteins. Results will then be visualized using gel electrophoresis. Detection of gametocytes using RT-PCR RT-PCR method will be used for detection of sub-patent gametocytemia during the dry season16, 17. Briefly, blood samples collected for RNA isolation and RT-PCR of *Pfs25* and *Pfg377* will first be left at room temperature for 30 minutes, to allow exflagellation and microgamete formation. The plasma and the buffy coat will be removed and the red blood cells stored at -70°C. Total RNA will be isolated using RNA isolation kits. RT-PCR of RNA will then be carried out.   - - 1. **Study definitions (eg case definition) should be mentioned.**   Clinical malaria includes those with microscopically diagnosed *P. falciparum* and clinical symptoms.  Sub-patent parasitaemia includes those detected positive by PCR  Gametocyte reservoirs include those detected positive by the RT-PCR.  **6.8.Data Management and Statistical Analysis**  (Describe the overall plan and tests used for data analysis and statistical package used)  The efficiency of the two treatment regimens will be assessed by comparing the proportions detected positive for asymptomatic infections before and after treatment. Comparison will be done using chi-square test and the significance of the results will be measured by the *P-value*.  Malaria prevalence and percent of mortality will be determined from data collected during the transmission season survey. They will be used for evaluation of the intervention by comparing them between the two villages and with data of the previous transmission season for every village. Comparison will also be done by chi-square test.  The data will be analyzed using SPSS (Statistical Package for Social Science) version 10. |

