| 1. Ethical Considerations    1. Informed consent form (If needed, please attach extra documents)  - Preliminary meetings will be held with the community leaders to inform them about the project and its objectives and to ask for their permission and collaborating in passing the message to the community. - A signed informed consent form will be collected from householders stating their agreement to participate. Even within each household, blood samples will be collected from those who are willing to participate. - Blood samples will be collected by a qualified laboratory technician with experience of more than 15 years in this field. This will be done under supervision of a medical doctor. - Clinical investigations for all patients, including those with common diseases, during every survey will be carried out by a medical doctor. He will also be responsible for prescription of drugs and very close clinical monitoring specially for those who will be given antimalarial drugs. - The principal investigator is committed to provide drugs for malaria and for other common diseases to those who will be detected sick during the surveys.      - 1. Institutional ethical clearance   Do you have an ethical review board in your institution: Yes [ ] No [ X ]  If no, then the ethical clearance of the Ministry of Health could be accepted.  (To be amended in case of initial acceptance by the selection committtee) |
| 1. Other funding agency   Is your study funded by another funding agency: Yes [ x ] No [ X ]  (specify the agency and available funds)  TC grant from the IAEA. |

| **12. Timeframe of research activities** (please indicate the activities to be conducted and check the corresponding month) | | | | | | | | | | | | |
| --- | --- | --- | --- | --- | --- | --- | --- | --- | --- | --- | --- | --- |
| Activity | 1st QUARTER | | | 2nd QUARTER | | | 3rd QUARTER | | | 4th QUARTER | | |
|  | M1 | M2 | M3 | M4 | M5 | M6 | M7 | M8 | M9 | M10 | M11 | M12 |
| ***Transmission season of 2003 survey*** |  |  |  |  |  |  |  |  |  | **X** | **X** |  |
| ***Dry season field survey*** |  |  | **X** |  |  |  |  |  |  |  |  |  |
| ***Nested PCRs*** |  |  |  | *X* | *X* |  |  |  |  |  |  |  |
| ***Samples for RT-PCR*** |  |  |  |  | ***X*** |  |  |  |  |  |  |  |
| ***RT-PCRs*** |  |  |  |  | X | X |  |  |  |  |  |  |
| ***Submission of the Progress Report*** |  |  |  |  |  | X |  |  |  |  |  |  |
| ***Pre-transmission field survey*** |  |  |  |  |  |  | *X* |  |  |  |  |  |

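### The efficacy outcome in section 6.8 is limited to asymptomatic infections, so read literally it leaves out a symptomatic slide-positive participant and does not match the endpoint the trial is sized on

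*Protocol*

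**What the plan says.** Section 6.8 gives the efficacy outcome in one sentence: "The efficiency of the two treatment regimens will be assessed by comparing the proportions detected positive for asymptomatic infections before and after treatment". The test is a chi-square test.

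Other parts of the protocol bear on this sentence:

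- **Study definitions (end of 6.7).** Clinical malaria requires both a positive film for *P. falciparum* and symptoms. Sub-patent parasitaemia is defined by PCR and the gametocyte reservoir by RT-PCR.
- **Objectives (5.2).** The two combinations are to be tested for clearing sub-patent parasitaemia and gametocytaemia.
- **Study design (6.4).** The treatment trial takes in malaria cases as well as asymptomatic carriers. Participants are to be "followedup on days 3, 7 and 14 to confirm the clearance of" sub-patent parasitaemia and gametocyte carriage.
- **Sample size (6.5.2).** The trial is sized on "gametocyte prevalence detected by RT-PCR after treatment is 20% or more on day 3 in AS/SP combination and 5% or less in AS/SP + PQ".
- **Laboratory methods (6.4, 6.7.1, 6.7.2).** For nested PCR, parasite "DNA will be extracted from filter papers of microscopically negative blood samples". Tubes for RT-PCR are drawn only from people who are positive by PCR.
- **Ethical considerations.** "The principal investigator is committed to provide drugs for malaria and for other common diseases to those who will be detected sick during the surveys".

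**The concern.** An efficacy outcome should count the failures the treatment is meant to prevent. As worded, 6.8 counts a carrier who remains faintly PCR-positive without symptoms, but not a participant whose infection has become patent and symptomatic. That is the wrong way round for a trial of clearance. The outcome also does not name the gametocyte endpoint on which the trial is sized, so the planned analysis and the planned sample size concern different quantities.

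What is at stake is whether the reported clearance proportions describe everyone randomised. The protocol intends to recommend the better regimen to the national control programme, so the outcome behind that recommendation should have one clear meaning.

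**Working it through.** No figure in the plan can be recomputed for this point. The 20%, 5% and 55 per arm in 6.5.2 are used here only to identify the sized endpoint. Whether 55 per arm gives the stated power is a separate question on which nothing below depends.

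**Step 1. Classify each possible state at a follow-up visit by the protocol's own definitions.**

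| State at the visit | Definition met (6.7) | In the 6.8 numerator, read literally? |
| --- | --- | --- |
| Film negative, PCR positive, no symptoms | Sub-patent parasitaemia | Yes |
| Film positive, no symptoms | Not clinical malaria | Yes, an infection without symptoms |
| Film positive, symptoms | Clinical malaria | No |
| Film negative, PCR positive, symptoms | Sub-patent parasitaemia, not clinical malaria | Not settled |
| RT-PCR gametocyte positive | Gametocyte reservoir | Not named in 6.8 |

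The third row is the clear omission. The fifth is the mismatch with 6.5.2.

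**Step 2. Compare 6.8 with the aims.** Sections 5.2 and 6.4 speak of clearance, and 6.5.2 of gametocyte prevalence by RT-PCR. None is limited to people without symptoms. Section 6.4 admits malaria cases, who by definition have symptoms and so could not be positive for the 6.8 outcome even before treatment. Section 6.6 enrols people who were PCR-positive, and 6.4 sends only film-negative samples to PCR, so it is unclear whether malaria cases are randomised at all. If they are not, the conflict at baseline falls away, but the omission at follow-up remains.

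**Step 3. Follow the laboratory sequence.** It is: film; PCR if the film is negative; RT-PCR blood if PCR is positive. Section 6.4 states it for the dry-season survey, and no sequence is given for days 3, 7 and 14. If it were applied unchanged at those visits, a film-positive participant would get no PCR. RT-PCR depends on whether PCR-positive refers to that visit or to enrolment. On the first reading there is no RT-PCR result; on the second there is.

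**Step 4. Ask whether size or direction can be derived.** Let an arm have *N* participants seen at a visit, *x* truly positive, of whom *s* are slide-positive with symptoms.

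- If the *s* are scored as not positive, the observed proportion is (*x* − *s*)/*N*. If they are dropped, it is (*x* − *s*)/(*N* − *s*). The protocol states neither rule.
- With equal *N* and the first rule, the difference between arms A and B moves by −(*s*A − *s*B)/*N*. Its sign depends on which arm has more such participants.
- The before-and-after change is also undetermined. A malaria case at day 0 is outside the numerator before treatment, and would enter it afterwards if symptoms resolved while PCR stayed positive.

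The documents give no value for *s* in either arm. The 20% and 5% cannot stand in for it: they are day-3 gametocyte prevalences, not rates of symptomatic failure.

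**The case against.** The strongest reply is that this is loose wording and little more. Several parts of that reply stand.

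- **The laboratory sequence belongs to the survey.** The follow-up sentence in 6.4 is separate and names no sequence. Randomised participants were PCR-positive at enrolment, so the limit on RT-PCR tubes need not exclude them. This stands, and is why the loss of results is put only as a conditional risk.
- **Nobody is said to be scored as cleared or lost.** A reader might infer that the worst failures are counted as successes. No passage says so. A slide-positive participant without symptoms still counts under 6.8, and a positive film is itself a detected infection.
- **Other malaria drugs.** A reader might infer that ill participants are re-treated within days 3 to 14 and their later negative samples credited to the assigned regimen. The commitment to provide drugs is tied to the surveys, which the timeframe lists apart from treatment and drug testing. The ethics section does promise close monitoring of those given antimalarials, so such use is possible, but it is not stated. It could not change a day-3 sample already taken.
- **Events may be few.** Section 6.4 places the return of symptoms in the malaria season, October to December, and the timeframe puts treatment in months 7 to 9.
- **No reason for an imbalance.** Both arms receive artesunate and S/P, and primaquine is added against mature gametocytes. The documents do not suggest more symptomatic failures in one arm, so a bias towards no difference cannot be presumed.
- **An analysis plan may exist.** Handling of missing results and other drugs may properly sit there.

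The reply does not dispose of the main point. The outcome is not left open for a later document: 6.8 fixes it, in words that conflict with 5.2, 6.4 and 6.5.2.

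**Conclusion.** The point holds as an inconsistency in the definition of the outcome. Section 6.8 limits efficacy to asymptomatic infections. Read literally, this leaves out a participant who is slide-positive with symptoms at follow-up, and it does not name the RT-PCR gametocyte endpoint on which the trial is sized. The risk of missing PCR or RT-PCR results for film-positive participants is secondary, and arises only if the survey sequence is reused at follow-up.

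No size can be given. The number of symptomatic slide-positive participants is not stated for either arm and may be zero, in which case this omission has no numerical effect. The direction of any bias in the arm comparison is likewise unknown. The case for correction rests on the wording alone, and it is a modest correction that should be made.

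**What to change.** **In 6.8,** replace the restriction to asymptomatic infections with two outcomes, each compared between the randomised arms:

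1. RT-PCR gametocyte positivity on day 3, the sized endpoint, with days 7 and 14 as further time points.
2. *P. falciparum* infection by film or PCR, with or without symptoms.

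**In 6.7,** state that at each follow-up visit RT-PCR is run on every randomised participant whatever the film result or symptoms, and that a positive film counts as infection.

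**In the follow-up record,** note any antimalarial taken outside the assigned regimen, so that its effect on the day 7 and day 14 results can be shown in a sensitivity analysis. How such participants are scored in the main analysis is a choice among several defensible strategies and can be left to the analysis plan. Nothing here alters who is treated, when or with what.

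Sections 6.4 and 6.6 should also be reconciled on whether malaria cases are part of the randomised comparison.

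The cost is a few sentences, a few extra assays, and possibly a slightly less favourable clearance figure.

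### The only efficacy analysis in section 6.8 is before versus after treatment; read literally, it does not compare the randomised arms on the day-3 RT-PCR gametocyte endpoint that sizes the trial

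*Protocol*

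**What the plan says.** **Analysis (Protocol 6.8).** "The efficiency of the two treatment regimens will be assessed by comparing the proportions detected positive for asymptomatic infections before and after treatment". The test follows: "Comparison will be done using chi-square test and the significance of the results will be measured by the" *P*-value. No assay, visit day or between-arm efficacy comparison is named. The one explicit comparison between groups in 6.8 is between the two villages, for malaria prevalence and mortality in the transmission season.

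**Sample size (Protocol 6.5.2).** "A trial with 55 subjects on each arm would have 90% power", with alpha 0.05 and an allowance of 10% for dropout. The contrast is given as one between the arms: "to detect a difference between treatment groups". The rate assumed without primaquine is worded as "gametocyte prevalence detected by RT-PCR after treatment is 20% or more on day 3 in AS/SP combination". With primaquine added, the assumed rate is 5% or lower.

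**Enrolment and allocation (Protocol 6.6).** "Persons who were positive by PCR in the dry season will be enrolled in the study". The list is sorted by village and age, and individuals are allocated in blocks of 12.

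**Expected difference between arms (Protocol 6.3).** Both arms receive artesunate and SP. Of the third drug the protocol says: "The addition of premaquine is expected to clear mature gametocytes".

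**Objectives and follow-up (Protocol 5.2 and 6.4).** Clearing sub-patent parasitaemia and clearing gametocytaemia are both named, and both are followed on days 3, 7 and 14.

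**The concern.** The trial exists to identify the appropriate drug (5.1), and the result is meant for the national control programme. Only the randomised contrast between the arms can support that choice. The stated rule instead sets each person's later result against the earlier one.

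Both regimens contain artesunate and SP, so positivity should fall in both arms whether or not they differ. Two significant falls would say nothing about relative merit. One significant and one non-significant fall could be misread as a drug difference. The gametocyte outcome, on which 6.3 and 6.5.2 expect the arms to separate, would have no stated test.

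**Working it through.** **1. The plan's own figure.** Inputs from 6.5.2: p1 = 0.20, p2 = 0.05, alpha 0.05 (taken as two-sided; the protocol does not say), power 90%, 55 per arm including 10% loss, so 55 × 0.9 = 49.5, about 50 evaluable.

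n = [z(α/2)·√(2·p̄·q̄) + z(β)·√(p1q1 + p2q2)]² / (p1 − p2)², with p̄ = 0.125.

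- 1.960 × √0.21875 = 0.9167; 1.2816 × √0.2075 = 0.5838.
- n = (0.9167 + 0.5838)² / 0.0225 = 100.1, so 101 evaluable per arm; 101 / 0.9 gives 113 with loss.
- One-sided 0.05: 82 evaluable, 92 with loss.

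The stated 55 is not reproduced. That is a separate matter, but it bears on the corrected analysis (step 5). The calculation does confirm that 6.5.2 is a two-group comparison.

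**2. Sections side by side.**

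| | 6.5.2 | 6.8 |
|---|---|---|
| Contrast | between treatment groups | before and after treatment |
| Outcome | gametocyte prevalence by RT-PCR | asymptomatic infections (no assay; not among the study definitions) |
| Time | day 3 | not stated |
| Data structure | two independent groups | same people twice, if read literally |

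**3. What a before/after test shows when the regimens are identical.** The protocol gives no baseline gametocyte prevalence, so 40% to 80% is assumed, with 20% after treatment in both arms and n = 50. Before and after are drawn independently, as the ordinary chi-square test treats them. The chance that one arm is significant is approximately

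Φ{ [(p0 − p1)·√n − 1.960·√(2·p̄·q̄)] / √(p0q0 + p1q1) }.

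At baseline 50%: (0.30 × 7.071 − 1.960 × √0.455) / √0.41 = (2.121 − 1.322) / 0.640 = 1.25, so Φ = 0.894. Both arms significant: 0.894² = 0.80. Exactly one: 2 × 0.894 × 0.106 = 0.19. Simulation (20,000 trials) gives:

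| Baseline | Identical (20%, 20%): both significant | Identical: exactly one | True 20% vs 5%: both significant |
|---|---|---|---|
| 40% | 36% | 48% | 59% |
| 50% | 80% | 19% | 90% |
| 60% | 98% | 2% | 99% |
| 80% | 100% | 0% | 100% |

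From a 50% baseline upward, the pattern is nearly the same whether or not the regimens differ. At 40%, identical regimens split into one significant and one non-significant arm in about half of trials.

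**4. The test, under the literal reading.** Take 50 people, 20 positive before (40%) and 10 after (20%), with nobody newly positive.

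- Ordinary chi-square: 100 × (20×40 − 30×10)² / (50×50×30×70) = 4.76, p = 0.029.
- McNemar on the 10 against 0 discordant pairs: (10 − 0)² / 10 = 10, p = 0.002.

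The unpaired test gives the wrong p-value. The paired test corrects that but still does not compare the arms.

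**5. The comparison that 6.5.2 describes.** Two-sided power for 20% against 5%:

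- n = 50: (0.15 × 7.071 − 0.9167) / 0.4555 = 0.316, power 62%.
- n = 55: (0.15 × 7.416 − 0.9167) / 0.4555 = 0.430, power 67%.

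**The case against.** The strongest defence is that the sentence in 6.8 is loosely worded. Its subject is the two regimens, so it may mean comparing their proportions positive at each time. The sample size and the randomisation point that way, and chi-square is then a suitable test. Clearance of parasitaemia is a named objective, and the term asymptomatic infections may be meant to include gametocyte carriage. A separate analysis plan may also hold the detail.

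Much of this stands. The contrast may be bad drafting and not bad intent, and the paired-data fault arises only under the literal reading. But where the authors want a comparison between groups, in the village paragraph of 6.8, they say so. On the kindest reading the section still names neither the RT-PCR endpoint nor day 3. The point rests on what 6.8 states, not on what it leaves out for an analysis plan.

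Four stronger readings are tempting and not supported:

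- *That the trial cannot answer its question.* Randomisation and follow-up on days 3, 7 and 14 would allow the right analysis if RT-PCR is done at those visits.
- *That infection is the wrong outcome.* It is an objective, and the nested PCR targets gametocyte genes, so primaquine might affect it. It is incomplete, not wrong.
- *That everyone is positive at baseline by selection.* Screening PCR is in months 4 and 5, with a further survey in month 7 before treatment. If that survey supplies the earlier value, positivity may be below 100%. Gametocyte carriers are sought among the PCR-positives, so their share is unknown.
- *That natural clearance alone would make both arms significant.* No clearance rate is given, and 6.1 says that some sub-patent infections last through the dry season.

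**Conclusion.** The concern holds as a mismatch inside the protocol. Followed literally, 6.8 does not test the randomised contrast, omits the endpoint and day on which 6.5.2 sizes the trial, and uses an independent-samples test on repeated measurements. A before/after result, significant or not, cannot show which regimen is better.

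The size depends on a baseline gametocyte prevalence that the protocol does not give. Over an assumed 40% to 80%, with identical regimens, 50 per arm and 20% positive afterwards, both arms are significant in 36% to 100% of trials. These figures treat before and after as independent; within-person correlation would change them, but not the conclusion that the arms are never compared. The mismatch in endpoint and day needs no assumption and remains under either reading of the sentence.

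**What to change.** Replace the efficacy sentence in 6.8 with wording such as: *The primary efficacy analysis compares the proportion RT-PCR gametocyte-positive on day 3 between AS+SP and AS+SP+PQ, as randomised, by chi-square or exact test, with the risk difference and 95% confidence interval. Gametocyte positivity on days 7 and 14, and PCR parasitaemia, are secondary between-arm comparisons. Within-arm change is descriptive; if tested, McNemar's test is used.*

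Align section 12 as well. It lists RT-PCR sampling in month 5 and RT-PCR in months 5 and 6, but treatment and drug testing in months 7 to 9, with no RT-PCR line after treatment. Section 6.7.1 limits RT-PCR blood to PCR-positive people; it should say that all randomised participants are sampled at follow-up.

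The wording costs one paragraph and a timetable line. If the follow-up in 6.4 already includes RT-PCR, no new data are needed. If not, the added work is up to 2 × 55 = 110 samples for day 3, or 330 for all three visits. Section 6.5.2 should be rechecked at the same time: correcting the analysis alone leaves two-sided power at about 62% to 67%, against the stated 90%.

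### Section 6.8 tests efficacy before against after treatment in people enrolled for being PCR positive, so missed detection and spontaneous loss count as drug clearance

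*Protocol*

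**What the plan says.** - **Entry.** Section 6.6: "Persons who were positive by PCR in the dry season will be enrolled in the study for measuring the efficacy of each combination". The PCR step in 6.4 is applied to film-negative people: "Samples detected negatives by blood films will be screened by conventional nested PCR". No second positive is required. Section 6.4 also describes a wider group: "A treatment trial will then be carried out on malaria cases and asymptomatic carriers at the end of the dry season".
- **Definitions (6.7).** "Sub-patent parasitaemia includes those detected positive by PCR". Gametocyte carriage rests on a different assay: "Gametocyte reservoirs include those detected positive by the RT-PCR".
- **Follow-up (6.4).** Visits are on "days 3, 7 and 14 to confirm the clearance of" sub-patent parasitaemia and gametocyte carriage. The follow-up assay for parasitaemia is not named, though the definition implies PCR.
- **Allocation (6.3, 6.6).** Two active combinations are allocated by "restricted randomization with a block size of 12 in Stata version 7". There is no untreated arm.
- **Sample size (6.5.2).** 55 per arm, for a difference between the groups in RT-PCR gametocyte prevalence on day 3 (20% against 5%).
- **Analysis (6.8).** The regimens are assessed by "comparing the proportions detected positive for asymptomatic infections before and after treatment", using chi-square and its P-value.

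**The concern.** Sections 6.5.2 and 6.6 set up a randomised comparison between arms. Section 6.8 then words the efficacy test as a change over time. That change is measured in people selected for a positive result, so the proportion can only stay at 100% or fall. It will fall if the assay misses some persisting infections, which is plausible because these infections are already too sparse for microscopy. It will also fall if some infections end by themselves. The timetable adds to this: the dry-season survey is in month 3 and treatment starts in month 7, so if the screening result serves as the before value, up to four months or more of natural loss is credited to the drug.

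Without an untreated arm, nothing in the before/after comparison separates these losses from a drug effect. Each regimen's absolute clearance is overstated, and a significant P-value does not show that the regimen worked. The protocol expects the study to identify a highly effective combination, and that is a statement about absolute clearance.

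**Working it through.** **Inputs.** Arm size 55 and 10% loss come from 6.5.2. The before value of 55/55 follows from entry under 6.6. The repeat-sample sensitivity s is an assumption, because the documents give none; the range 0.70 to 0.95 is shown. The test is chi-square at 0.05, as in 6.8.

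**The plan's own figure.** The 55 per arm is used here only as the arm size. It does not reproduce as stated, which is a separate matter. For 20% against 5%, two-sided 0.05 and 90% power, the mean proportion is 0.125, and

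n = [1.96√(2×0.125×0.875) + 1.2816√(0.16+0.0475)]² / 0.15² = 101 per arm; 101/0.9 = 113 after 10% loss.

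**When the before/after test becomes significant.** Let x of n persistently infected people test negative afterwards. With n/n before and (n−x)/n after, the uncorrected statistic simplifies to

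χ² = 2n·x / (2n − x).

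For n = 55: x = 3 gives 330/107 = 3.08, and x = 4 gives 440/106 = 4.15. The critical value is 3.84, so four negatives out of 55 are enough.

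**How often that happens with no drug effect.** Take x ~ Binomial(55, 1−s). For s = 0.95, P(x = 0, 1, 2, 3) = 0.060 + 0.172 + 0.245 + 0.228 = 0.705, so P(x ≥ 4) = 0.295. In the same way:

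| Assumed s | False clearance, 1−s | Rejection, n = 55 | Rejection, n = 50 |
|---|---|---|---|
| 0.95 | 5% | 30% | 24% |
| 0.90 | 10% | 81% | 75% |
| 0.80 | 20% | 99.8% | 99.4% |
| 0.70 | 30% | 100% | 100% |

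The last column uses about 50 evaluable per arm (55 × 0.9 = 49.5). Spontaneous loss would add to these figures.

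**Continuity correction.** 6.8 does not say whether one is used. With it, x = 5 gives 110(275−55)²/(55²×105×5) = 3.35 and x = 6 gives 110(330−55)²/(55²×104×6) = 4.41, so six negatives are needed. P(x ≥ 6) for n = 55 is then 6%, 48%, 98% and 100%. At s = 0.95 the excess largely disappears; at 0.90 and below it does not.

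**Where the error comes from.** If the before value is instead a new, unselected sample with the same sensitivity, both proportions are Binomial(n, s)/n and rejection is 4% to 5% for s from 0.70 to 0.95. Fixing before at 100% by selection is therefore what inflates the test.

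**The comparison between arms.** Equal misses multiply both prevalences by s. If they are equal, they stay equal, so there is no false difference. A true 20% against 5% shrinks, for example to 16% against 4% at s = 0.80. With 50 per arm, power falls from 62% to 60%, 57%, 52% and 46% at s = 0.95, 0.90, 0.80 and 0.70. Misses cost power here but do not create an effect.

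**The case against.** Several points on the other side stand.

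- **The randomised contrast.** A reader might infer that the trial's comparison of the two drugs is biased. It is not biased under the null, because misses fall on both arms alike.
- **The powered outcome.** A reader might infer that entry and outcome always use the same assay. For parasitaemia this is only implied. For gametocytes it is wrong: entry is by nested PCR and the outcome is RT-PCR, so baseline gametocyte prevalence is not fixed at 100%.
- **Who enters.** Section 6.4 also admits malaria cases, so the argument applies to those who enter by PCR, not to every treated person.
- **Single negatives.** A reader might infer that the protocol accepts one negative as final even if the next visit is positive. It does not say so. Three visits are planned, proportions at each visit would show a later positive, and the rule for combining visits may properly sit in the SAP.
- **A fresh baseline.** It would bring the missed-detection error back to about 5%. The timetable lists a pre-transmission survey in month 7, but its sampling is not described and 6.8 does not name it as the before value.
- **The recommendation.** The proposed national use is conditional and concerns the dry-season strategy, including its effect on morbidity. It does not rest on PCR clearance alone.

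It can also be argued that 6.5.2 makes the between-arm comparison the intended one. That may be so, but the efficacy test actually written in 6.8 is before against after. This is a stated analysis, not a detail left to the SAP.

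**Conclusion.** The point holds for the before/after test of sub-patent parasitaemia among people who enter by PCR. As written, that test can be significant for a regimen with no effect: about 30% to 100% of trials per arm for assumed sensitivity 0.95 to 0.70 without continuity correction, and 6% to 100% with it. Apparent clearance with no drug effect is 5% to 30% on one negative sample. These sizes rest on the assumed sensitivity, on independent results between people and on no spontaneous loss. The structural point needs none of these: before is 100% by selection, and no untreated arm absorbs the later losses.

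A figure of 81% at sensitivity 0.95 arises only if both arms are pooled (n = 110). Section 6.8 assesses two regimens, so the per-arm 30% is the fairer figure. The documents do not support extending the point to the randomised comparison or to baseline RT-PCR prevalence.

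**What to change.** In 6.8, replace the before/after chi-square as the test of efficacy with a comparison between the randomised arms of the proportions positive at each planned visit: RT-PCR gametocytes on day 3, as in 6.5.2, and PCR parasitaemia and RT-PCR gametocytes on days 7 and 14. Report within-arm before/after change descriptively only, and state that it includes missed detection and spontaneous loss.

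Clearance confirmed by negatives on both day 7 and day 14 may be added as a sensitivity analysis. If misses are independent, it cuts false clearance from 1−s to (1−s)², that is to 0.25%, 1%, 4% and 9% over the same range of s. It should not be the main definition. Someone positive on day 7 and truly clear by day 14 would count as a failure, although the background section expects gametocytes to decline gradually. If a missed visit also counts as not cleared, the planned 10% loss could lower reported clearance by up to 10 points.

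The cost is a few sentences in 6.8, with no new visits, samples or participants. The protocol gives up a P-value for each regimen's own before/after change, and efficacy then rests on the contrast between arms, with the limited power shown above.
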